## Discussion

To date, this is the first study to evaluate the effectiveness and cost-effectiveness of a short CBT-based treatment provided by MHNPs for patients with undifferentiated somatoform disorder in primary care versus usual care. The aim of the treatment is to improve physical functioning by increasing problem-solving skills to cope with consequences of the physical symptoms and with everyday problems in general. We assume that higher physical functioning and quality of life will result in lower health care-related and work-related costs.

A strength of this study is that the intervention is provided within the patients’ own general practices. Given the prevalence of USD and the large societal costs that accompany this disorder, there is an urgent need to provide easily accessible and affordable treatment for patients with USD. A previous study showed that providing psychological help in general practice was effective in improving quality of life [18]. However, the intervention in this study was conducted in a group setting by psychologists from secondary care who offered treatment to patients in general practice. This might not always be feasible and time-efficient. MHNPs, working in general practices and trained in providing (short) psychological treatment, are in a much more convenient position to help patients.

Furthermore, receiving psychological treatment in the patients’ general practice may create a safe and low-threshold environment for patients with USD, especially those who would otherwise not seek psychological help in the mental health care setting. Also, by focussing on the consequences and not on the causes of physical symptoms, the possible struggle about the cause of the symptoms is avoided. Regardless of the cause, patients suffer from consequences of USD. This approach may create more acceptance from the patients.

By testing our intervention directly within general practices and with MHNPs who are already employed there, this study has a high clinical relevance. If successful, the intervention is likely to be easily implemented in daily practice as the number of MHNPs employed in the general practices is growing. This is especially relevant in The Netherlands, as more emphasis is being placed on provision of mental health care services in general practice as a result of organisational changes in health care services.

Additionally, the current intervention combines a cognitive behavioural theoretical framework with PST intervention techniques for somatoform disorders. To date, PST has been widely investigated in depression [32, 58, 59] but rarely in somatoform disorders. One preliminary study containing 11 subjects who received PST found that PST was acceptable to patients and reduced symptoms, hypochondriacal preoccupation and psychiatric morbidity [35]. Another study investigated PST in 162 patients and found a positive impact on symptoms, functioning and costs, but in this study PST was combined with other CBT techniques [18].

A possible limitation to our study is that we use the diagnosis undifferentiated somatoform disorder (USD) as defined by the DSM-IV. The fifth edition of the DSM (DSM-5) has a new classification for the previous category somatoform disorders. Previously, the category of somatoform disorders included somatization disorder, undifferentiated somatoform disorder, conversion disorder, pain disorder, hypochondriasis, body dysmorphic disorder and somatoform disorder not otherwise specified. All of these somatoform disorders except hypochondriasis, body dysmorphic disorder and conversion disorder have now been categorised under somatic symptom disorder (SSD). Furthermore, for the classification of SSD the somatic symptoms do not have to be medically unexplained. Our study was designed and funded before DSM-5 was introduced. SSD is a new DSM-5 classification and issues such as its usefulness and accuracy are currently a topic of debate in the field in addition to proposals for modifications of the criteria for SSD [60–62]. Moreover, since its introduction, the DSM-5 has not yet been widely used in research and practice, and no appropriate diagnostic instrument equivalent to the SCID or the Mini International Neuropsychiatric Interview (MINI) was available at the time of recruitment of patients. Therefore, for practical reasons it was impossible to diagnose patients reliably and validly according to the DSM-5. Recently the Health Preoccupation Diagnostic Interview (HPDI), a new structured diagnostic interview for the classification of somatic symptom disorder and illness anxiety disorder, has been developed by Axelsson and colleagues [63]. However, this diagnostic interview has not yet been validated.

Another limitation is that, due to the nature of the intervention, it is not possible to blind patients, health care providers and researchers to treatment allocation.

A final point of consideration concerns the primary outcome measure, the physical component summary score (PCS) of the RAND-36. The PCS is a general physical functioning scale, comprising subscales measuring physical aspects of health. Because the PCS is a summary score, the total score may be somewhat insensitive to change, as potential changes on the separate subscales may not lead to a difference in the total score. This may make it more difficult to detect an effect on the PCS. However, several previous studies have successfully used the PCS scale as a primary or secondary outcome and were able to detect change [18, 64–67]. Despite potential shortcomings, we also chose the PCS as the primary outcome measure, because a more specific measure, such as the subscale ‘physical pain’ of the RAND-36, may focus on only a part of physical functioning, whereas we aim to investigate physical functioning in a more generic manner. After all, the aim of the intervention is not to reduce the symptoms, but to improve physical functioning as a whole. We will also separately investigate the changes on the separate subscales as a secondary outcome in order to see whether more specific changes take place.

Overall, if this study shows that the treatment is effective and cost-effective, the treatment could result in great benefits in primary care by making psychological treatments more available to patients with USD and providing broader treatment possibilities for primary care professionals. Quality of life of patients with USD may be improved and health care costs may be reduced.

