## Methods/design

This protocol was developed in accordance with the Standard Protocol Items: Recommendations for Interventional Trials (SPIRIT) Statement. For the SPIRIT Figure see Additional file 1 and for the SPIRIT Checklist see Additional file 2. We will conduct a parallel-group, multicentre, cluster randomised controlled trial in 39 primary care centres (a list of the participating centres is provided in Additional file 3). Cluster randomisation will take place at the MHNP and general practice level in order to avoid contamination between the intervention and control conditions. Clusters will be composed by matching MHNPs to all participating general practices where the MHNP works and to all other MHNPs who also work in these general practices. The entire cluster consisting of one or more MHNPs and general practices will then be randomly assigned to the intervention or to care as usual (CAU) group, prior to the inclusion of patients. An independent statistician, not involved in the selection of the practices and MHNPs, will carry out the randomisation. In order to balance the size of the intervention and CAU groups, randomisation will be stratified according to cluster size (small: less than 5000 patients, and large: 5000 patients or more). Assessments will take place at baseline (T0), during the intervention period at approximately 2 months (T1), directly after the intervention period at 4 months (T2), at 8 months (T3) and at 12 months (T4) after baseline.

This study is registered at the Dutch Trial Registry (NTR4686) and was approved by the VU Medical Center Ethics Committee. It will be conducted according to the principles of the Declaration of Helsinki (version 2013). Important protocol modifications will be communicated with the Dutch Trial Registry and the VU Medical Center Ethics Committee.

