### Inclusion procedure

The researchers and GPs will select adult patients (aged 18 years or older) from the GP’s electronic database, who consulted the GP with one or more symptoms from the Robbins list [26] (Table 1) at least twice in the previous 3 months. The presented symptom does not necessarily have to be the same for each visit. The Robbins list consists of 23 physical symptoms that are associated with functional somatic syndromes. The symptoms on this list are likely to be medically unexplained if they lack an accompanying ‘diagnostic’ or ‘disease’ International Classification of Primary Care (ICPC) code (i.e. ICPC code >70). Following this step, the participating GPs will check the selected patients for exclusion criteria in order to, for example, avoid inclusion of patients with actual somatic pathology.

**Table 1 Tab1:** Symptoms from the Robbins list [26]

1. Back pain
2. Joint pain
3. Extremity pain
4. Headaches
5. Weakness
6. Fatigue
7. Sleep disturbance
8. Difficulty concentrating
9. Loss of appetite
10. Weight change
11. Restlessness
12. Thoughts slower
13. Chest pain
14. Shortness of breath
15. Palpitations
16. Dizziness
17. Lump in throat
18. Numbness
19. Nausea
20. Loose bowels
21. Gas or bloating
22. Constipation
23. Abdominal pain

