Patients identified as potentially eligible will then receive brief information about the study and the Patient Health Questionnaire somatization scale (PHQ-15) [27] from their GP. Patients who are interested in participation in the study and who have a PHQ-15 score of 5 (low symptom severity) or higher will receive extensive study information. We chose the cut-off point for low symptom severity in order to make sure that patients with disabling somatic complaints are not wrongly excluded at this point. Patients will then be invited to participate in a clinical interview (Structured Clinical Interview for DSM-IV Axis I Disorders (SCID-I)) to assess DSM-IV criteria for USD. Trained members of the research team will administer the interview by telephone. Patients meeting the DSM-IV criteria for USD (the presence of one or more medically unexplained physical symptoms that last at least 6 months and significantly impair functioning/quality of life) will receive an Informed Consent Form. After completing the Informed Consent Form and sending it back to the researcher they will be included in the intervention or CAU group based on the allocation of the MHNP and general practice to which they belong. An overview of the inclusion procedure is provided in Fig. 1.

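### The protocol calls blinding of researchers impossible for a reason that does not reach the telephone interviewers who judge eligibility, so an avoidable risk of differential selection between arms remains

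*Protocol article*

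**What the plan says.** Methods/design states that each whole cluster of practices and mental health nurse practitioners (MHNPs) is "randomly assigned to the intervention or to care as usual (CAU) group, prior to the inclusion of patients". On who does this, it says: "An independent statistician, not involved in the selection of the practices and MHNPs, will carry out the randomisation".

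Inclusion procedure describes how patients come in. "The researchers and GPs will select adult patients (aged 18 years or older) from the GP’s electronic database", using listed symptoms, consultation frequency and the absence of a disease code. Next, "the participating GPs will check the selected patients for exclusion criteria". Interested patients must reach a fixed PHQ-15 score of 5. The diagnosis of undifferentiated somatoform disorder is then made by SCID-I: "Trained members of the research team will administer the interview by telephone". Among the criteria is that the symptoms "significantly impair functioning/quality of life". Consent follows, and the arm is that of the practice and MHNP to which the patient belongs.

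The Discussion lists as a limitation that, owing to the nature of the intervention, "it is not possible to blind patients, health care providers and researchers to treatment allocation". It does not connect this with recruitment.

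**The concern.** When clusters are allocated before individuals enter, concealing the randomisation list protects the allocation of clusters but not the choice of patients within them. Anyone who judges eligibility and can know the practice's arm may, without intending to, apply the criteria differently in the two arms. Two of the entry steps leave room for this: whether another disorder explains the symptoms (GP), and whether impairment is significant (interviewer).

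The protocol closes off the simplest safeguard by declaring blinding of researchers impossible. If the arms come to hold different kinds of patients, analysis by intention to treat does not repair it, because that principle governs how included patients are analysed and not who was included. A larger sample does not repair it either.

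**Working it through.** **1. Who decides, and does the stated reason cover them?**

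| Step (Inclusion procedure) | Decided by | Fixed rule or judgement | Does the nature of the intervention prevent blinding? |
|---|---|---|---|
| Database extraction | Researchers and GPs | Mostly fixed rule | Not needed for a fixed rule |
| Exclusion check | GP | Judgement | Hard to avoid: the MHNP works in the practice and, in the intervention arm, is trained for the trial |
| PHQ-15 of 5 or more | Score | Fixed rule | Not needed |
| SCID-I by telephone | Research team member | Judgement on impairment | No: before consent, by telephone, and not said to deliver treatment |
| Consent | Patient | Choice | Yes once treatment starts; when the patient learns the arm is not stated |

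The claim of impossibility therefore fails for one row, and it is a row that decides eligibility. Some researchers clearly must know the arm. Under Feasibility testing and ongoing supervision, a researcher listens to recorded treatment sessions, and intervention MHNPs may contact the researcher. The article does not say whether the same people hold the SCID-I interviews.

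**2. Timing.** Allocation precedes inclusion (Methods/design). No section says that screening was finished before allocation, or that interviewers are kept unaware of it. Trial status reports that data collection began in November 2015 and that recruitment was still running, so a change can still affect patients not yet screened.

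**3. The plan's own figures.** Inputs from the sample size section: difference 4, SD 10, two-sided 5%, power 80%, correlation 0.5 with two follow-up measurements, cluster size 4, ICC 0.05, dropout 20%.

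- One measurement: 2 × ((1.960 + 0.842) × 10/4)² = 98.1 per arm.
- Two measurements: 98.1 × (1 + 0.5)/2 = 73.6, so 74 (stated 74).
- Design effect: 1 + (4 − 1) × 0.05 = 1.15; 74 × 1.15 = 85.1 (stated 85).
- Dropout: 85/0.8 = 106.25 (stated 106).

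The sample size reproduces and is not in dispute.

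**4. What a bias would do, by assumption only.** With 85 analysed per arm, the standard error of the treatment contrast is 10 × √((2/85) × 0.75 × 1.15) = 1.42 PCS points. Let b be a net shift in that contrast caused by differential selection. The document gives no value for b. With no true effect, the rejection rate is Φ(b/1.42 − 1.96) + Φ(−b/1.42 − 1.96). With a true 4-point effect and a shift against the intervention, b is replaced by 4 − b.

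| Assumed shift b (points) | Rejection rate, no true effect | Power, true effect 4, shift against |
|---|---|---|
| 0 | 5% | 80% |
| 0.5 | 6.4% | 69% |
| 1 | 10.8% | 56% |
| 2 | 28.9% | 29% |
| 3 | 55.8% | 11% |

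Here b is a shift in the treatment contrast, not a gap in baseline PCS. The table shows how sensitive the test would be. It is no estimate of the bias in this trial.

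**The case against.** The strongest reply is that the article shows less than a critic might infer.

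- A reader might infer that all selection follows randomisation. The text ties allocation to inclusion, and Inclusion procedure uses that word for the step after consent. When the database extraction and GP check took place relative to allocation is not stated. This stands, although nothing says they were completed beforehand.
- A reader might infer that GPs, interviewers and patients all know the arm. No section says so. What can be said is that they can know it and that no safeguard is described.
- A reader might infer that T0 answers are coloured by knowledge of the arm. The order of T0 and disclosure is not given, and an article commonly leaves such detail to the full protocol. It is no fault of this document.
- A reader might set a baseline PCS gap against the 4-point target. The analysis compares change scores, so a fixed baseline gap does not carry over one-for-one. Only differences that alter the course of PCS, such as prognosis or motivation, would bias the contrast.
- Discretion is narrowed by the extraction rule, the PHQ-15 cut-off and the structured interview. Lack of blinding is openly declared, reasons for non-participation and the age and gender of non-responders are collected, and the CONSORT extension for cluster trials is cited.

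All of this limits the point, but none of it supports the claim that a telephone interviewer cannot be kept unaware of allocation.

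**Conclusion.** The point holds in a limited form. The statement that researchers cannot be blinded is too broad: its reason does not apply to SCID-I interviewers, who judge eligibility before consent and are not described as giving treatment. Together with allocation before inclusion, this leaves an avoidable risk of differential selection at the interview step. The GP's exclusion check carries a similar risk, but one that is harder to remove.

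This is a risk and not a demonstrated bias. Its size and direction cannot be derived from the document. The conclusion assumes that at least some interviews take place after the cluster is allocated and that interviewers are not already shielded from the allocation. If the full protocol shows otherwise, only the wording of the limitation needs correcting.

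**What to change.** 1. For patients not yet screened, have the existing SCID-I interviewers work without knowledge of the practice's allocation. Where feasible, assign interviews to team members not involved in training, recordings or MHNP support.
2. Where feasible, have the T0 questionnaire completed before the patient is told the arm. This is a precaution, not a correction of a stated error.
3. In the Discussion, limit the impossibility of blinding to patients, care providers and researchers involved in delivery or supervision. Name recruitment after randomisation as a possible source of bias.
4. Report by arm the numbers extracted, excluded by the GP with reasons, declined, and SCID-negative. Fixing or documenting a GP's exclusions does not remove bias if the GP already knows the arm, but it lets readers judge whether the arms were filtered alike.

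The cost is minor logistics during ongoing recruitment, some tabulation, and no extra staff. Patients already included gain only from the reporting, and the gain from item 1 is limited where interviewers already know the allocation.

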### Trial status

The collection of data started in November 2015. Study results are expected to be available in April 2018. The recruitment of participants was ongoing at the time of manuscript submission.

## Abbreviations

BIA: Budget impact analysis
CAU: Care as usual
CBT: Cognitive behavioural therapy
CBRQ: Cognitive and Behavioural Responses Questionnaire
CEA: Cost-effectiveness analysis
DSM-IV (or DSM-5): *Diagnostic and Statistical Manual of Mental Disorders-IV* (or *-5*)
EQ-5D-5L: EuroQol 5D – 5 level version
GP: General practitioner
HADS: Hospital Anxiety and Depression Scale
HPDI: Health Preoccupation Diagnostic Interview
HRQoL: Health-related quality of life
ICC: Intra-class correlation coefficient
ICERs: Incremental cost-effectiveness ratios
ICPC: International Classification of Primary Care
IPQ: Illness Perception Questionnaire
MHNP: Mental health care practitioner
MINI: Mini International Neuropsychiatric Interview
NHG: The Dutch College of General Practitioners (Dutch: Nederlands Huisartsen Genootschap)
NZA: the Dutch Healthcare Authority (Dutch: Nederlandse Zorgautoriteit)
PCS: Physical component score
PHQ-15: Patient Health Questionnaire somatization scale
PST: Problem-solving treatment
QALYs: Quality-adjusted life years
RAND-36: RAND-36-item Health Survey
SCID: Structured Clinical Interview for DSM-IV
SSD: Somatic symptom disorder
SPSI-R:S: Social Problem-solving Inventory Revised: Short Form
Tic-P: Trimbos and iMTA questionnaire on Costs associated with Psychiatric Illness
USD: Undifferentiated somatoform disorder
WAI-SF: Working Alliance Inventory-Short Form
